### Statistical analysis

Statistical analysis will be performed according to the intention-to-treat protocol; however, a per-protocol analysis will also be done. Thus, all randomized patients who have followed the Mediterranean diet for at least 2 weeks and who have the baseline measurements will be analyzed. With regard to missing data, the mean of each variable will be used to replace missing data. First, we will apply the Kolmogorov-Smirnov test to determine the normality of variables. In case of the non-normal distribution of a variable, a logarithmic transformation will be conducted. Independent sample’s *t*-test (or its non-parametric test Mann-Whitney *U*) will be used to compare the baseline values ​​of continuous variables between the two groups. Moreover, the chi-square test will be conducted to compare categorical variables. To examine the effect of the Mediterranean diet on the outcome variables, we will apply repeated measures ANOVA, in which the effect of time, intervention, and time*intervention interaction will be explored. In addition to the investigation of the crude means of variables in this analysis, we will compute adjusted means of outcome variables taking into account the baseline levels of the relevant variables. Changes in outcome variables will also be examined between the two groups using an analysis of covariance, in which the baseline values will be considered as covariates. Data will be analyzed using SPSS software version 26. *P*-value <0.05 will be considered as statistically significant.

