**Methods:**

This will be a randomized clinical trial involving men and women diagnosed with localized or advanced colorectal cancer-induced cachexia. In total, 40 patients with CC will be recruited based on inclusion criteria and then these patients will be randomly allocated to receive either a Mediterranean diet (*n* = 20) or only routine nutritional advice (*n* = 20) for 8 weeks. The primary outcome will be nutritional status, muscle mass and strength, and serum concentrations of inflammatory markers including interleukin-6 (IL-6), tumor necrosis factor-alpha (TNF-α), and high-sensitive C-reactive protein (hs-CRP). Moreover, we will consider serum albumin and total protein levels, complete blood count (CBC), and quality of life as the secondary outcomes. All outcomes will be measured at the beginning and end (the eighth week) of the study. We will assess participants’ adherence to the prescribed diets by using a 1-day food record in the second, fourth, sixth, and eighth weeks of the study.

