### Exclusion criteria

Patients who meet the following conditions will be excluded from the study and will not be included in the per-protocol analysis: (1) patients who die during the study; (2) patients with less than 60% adherence to the Mediterranean diet based on the prescribed energy and macronutrients; (3) individuals who change their eating route from oral feeding to enteral or parenteral feeding throughout the study; (4) patients that are not willing to continue the study for any reason; and (5) patients who change their treatment protocol during the study.

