### Study design

After obtaining informed written consent, all required measurements will be performed at the beginning of the study. Then, stratified block randomization will be done based on the type of cancer (colon or rectum) and BMI (≤23, > 23) using the www.randomization.com website. The statistician will fold the paper containing a randomization number and put them in the envelopes and write the code on them. The envelopes will be kept at the enrollment center. Then, for each qualified patient, the nutritionist randomly picks one of the envelopes after shuffling and allocates patients into control and intervention groups. It is not possible to blind study participants or staff in this study due to nutritional interventions. Nevertheless, the outcome assessor will be blinded to the group assignment.

Regarding colorectal cancer treatment, subjects with rectal cancer undergoing first-line radiotherapy and subjects with colon cancer undergoing first-line chemotherapy with capecitabine and oxaliplatin (CAPOX), 5-fluorouracil-leucovorin-irinotecan (FOLFIRI), 5-fluorouracil and oxaliplatin (FOLFOX), or capecitabine will be included [17]. As explained, people will be placed in separate blocks based on the type of cancer. The duration of the study for both intervention and control groups will be 8 weeks. Participants in the intervention group will receive a Mediterranean diet menu along with extra virgin olive oil, while participants in the control group will receive nutritional advice for cancer patients and dietary recommendations for weight gain. To assess participants’ adherence to the proposed diets, a 1-day food record will be used in the second, fourth, sixth, and eighth weeks of the study. Moreover, to encourage patients to follow the diet, all patients will be contacted weekly during the study. Participants will be asked to maintain their normal daily activities during the study. In addition, individuals’ physical activity will be monitored through completing a 1-day record in the second, fourth, sixth, and eighth weeks of the study. At the end of the study, all required measurements will be taken again in both groups. A Standard Protocol Items: Recommendations for Interventional Trials (SPIRIT) diagram for the trial schedule is indicated in Fig. 2.

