### Intervention

The main intervention in this study is the administration of a Mediterranean diet. The energy required by patients in the intervention group will be computed according to the recommendations of the ASPEN guideline [19]. First, we will start with 25 kcal per kg of the current body weight and then gradually will move over 2 weeks to 35 kcal. Energy will be divided as follows between the macronutrients [20]: 35% of calories from fat (less than 7% saturated, 10–15% PUFA and the rest from MUFA), 45% of calories from carbohydrates, and 20% of calories from proteins. Then, by emphasizing the recommended food groups in the Mediterranean diet, the supply of these macronutrients from different food groups will be considered. Based on these food groups, a weekly dietary menu will be written for each patient. The Mediterranean diet will be designed based on the following recommendations: the use of extra virgin olive oil for cooking salads and other foods (participants will be given “extra virgin olive oil” free of charge), consumption of two or more exchanges per day of vegetables, three or more exchanges per day of fresh fruit, three or more exchanges per week of legumes, two or more exchanges per week of fish or seafoods, and three or more exchanges per week of nuts or seeds will be highlighted. The use of white meats instead of red or processed meats will also be focused. There will be also some recommendations to limit the consumption of butter, cream, fast foods, sweets, and sugary drinks. To increase the adherence to the dietary intervention, all the dietary menus will be personalized based on dietary habits of each person in the study.

In the control group, routine nutritional recommendations about weight gain and prevention of weight loss in cancer patients based on the clinical guidelines [21] will be given as brochures. All the points in these brochures will be explained to patients orally in a training session. As mentioned above, this group of patients, like the patients in the intervention group, will be followed up during the study period.

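### The set described as intention-to-treat keeps only patients who followed the Mediterranean diet for at least 2 weeks, so it is not intention-to-treat and the main comparison can be biased

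*Protocol article*

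**What the plan says.** The Statistical analysis section opens with the principle: "Statistical analysis will be performed according to the intention-to-treat protocol; however, a per-protocol analysis will also be done". The next sentence, introduced as a consequence of that one, gives the working rule: "all randomized patients who have followed the Mediterranean diet for at least 2 weeks and who have the baseline measurements will be analyzed". The same section replaces missing values with the mean of the variable.

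The Exclusion criteria section describes patients who "will be excluded from the study and will not be included in the per-protocol analysis". It lists five grounds: death, "patients with less than 60% adherence to the Mediterranean diet based on the prescribed energy and macronutrients", a change of feeding route, unwillingness to continue, and a change of treatment protocol. None of them is a 2-week minimum.

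The control arm is not given the Mediterranean diet. Under Study design, "participants in the control group will receive nutritional advice for cancer patients and dietary recommendations for weight gain". The abstract describes 40 patients "randomly allocated to receive either a Mediterranean diet (*n* = 20) or only routine nutritional advice (*n* = 20) for 8 weeks".

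**The concern.** An intention-to-treat set is fixed by randomisation alone. Here membership depends on what a patient did in the first 2 weeks, and the condition is written in terms of a diet that only one arm receives. Patients who abandon the diet early would leave the intervention arm, while comparable control patients, who face no stated equivalent, would stay.

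Three things are at stake. The main comparison loses the protection of randomisation for every outcome. The result would carry a label it has not earned. And in a trial this small each excluded diet patient is 1/20 = 5% of that arm.

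**Working it through.** **1. Which set does the sentence define?** It follows directly from a sentence naming both analyses, so the grammar alone does not settle it. The Exclusion criteria section already ties five other grounds to the per-protocol analysis. The 2-week sentence therefore most naturally defines the intention-to-treat set. If it was meant for per-protocol, the two sections give different rules and the intention-to-treat set has no stated definition. The text needs correcting on either reading.

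**2. Whom does it filter?** Literally: every control patient fails, since none is assigned the Mediterranean diet, and no comparison remains. Sensibly: controls are all kept and only the diet arm is filtered. Neither is intention-to-treat.

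**3. The plan's own figure.** From Sample size calculation: S = 4.1, d = 3.9, two-sided α = 0.05, power 80%.

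n = 2 × (1.960 + 0.842)² × 4.1² / 3.9² = 17.35 per group. The article states 17, and 17 / 0.85 = 20. The figure is reproduced to within rounding, and this point does not depend on it. S and d supply the scale used below.

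**4. Size of the bias, simple form.** Suppose there is no true effect, a share f of the diet arm is removed, and those patients would score g PG-SGA points worse than the rest (a higher score is worse). The unadjusted bias toward the diet is f × g. The documents give neither f nor g.

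- f = 0.15, g = 4.1 (1 SD): 0.15 × 4.1 = 0.61 points; simulated two-sided type I error about 7%.
- g = 0: no bias, error 5%.
- g = −4.1 (early stoppers do better), f = 0.05 to 0.25: 0.2 to 1.0 points *against* the diet.

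**5. Size under the planned analysis of covariance.** Null simulation, 8,000 trials per case, 20 per arm, SD 4.1. Assumed: baseline-to-week-8 correlation 0.5; k of 20 diet patients removed with sampling weight exp(0.75 z) or exp(1.5 z), which is 2.1 or 4.5 times the weight per SD of worse z.

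Where z is the **week-8 outcome**:

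| Removed (k) | Spurious gain for the diet (points) | Two-sided type I error |
|---|---|---|
| 2 | 0.23–0.38 | 5.8–6.6% |
| 3 | 0.34–0.55 | 6.5–8.0% |
| 4 | 0.47–0.75 | 6.9–10.4% |

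Repeat runs agreed to within a few hundredths of a point and under one percentage point of error rate. The largest gain is 0.75 / 3.9 = 19% of the planned difference.

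Where z is **baseline severity**, with the same weights: bias at most 0.03 points and error 4.8–5.2%, because the covariate absorbs the selection.

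**6. Would restoring the patients be enough?** Only if their week-8 values are measured. Under the outcome-related cases of step 5, putting the patients back and filling their outcome with the overall mean gives 0.27–0.87 points and 5.8–13% error. With the arm mean it gives 0.29–0.99 points and 6.6–19%. Neither is better than the filter.

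**The case against.** The strongest reply is that the harm is not shown. A reader might infer that the result *will* favour the diet, because sicker patients stop first. The documents do not support that as fact. They give no early stopping rate and no outcome for those who stop, and step 5 shows that being sicker at baseline is not enough: stopping must track the week-8 outcome beyond what baseline predicts. This objection stands, and it limits the claim to a possible bias.

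A reader might also infer that the condition removes patients who cannot tolerate the energy build-up, since energy starts lower and "then gradually will move over 2 weeks to 35 kcal". The timing does coincide, but week 2 is also the first food record, and the article does not link the condition to tolerance.

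It is also fair to say that the sentence may be loose drafting, and that a 2-week minimum could sit alongside the listed per-protocol exclusions. So a per-protocol reading is not impossible, only less natural. Loose drafting is a reason to correct the sentence; it does not make the set intention-to-treat.

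What remains on the other side is plausibility of direction. These patients have cachexia and are on chemotherapy or radiotherapy. PG-SGA itself scores food intake and gastrointestinal problems. Participants and staff know the allocation. A tilt toward the diet is the likelier one.

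**Conclusion.** The contradiction is clear and should be corrected: the section announces that "Statistical analysis will be performed according to the intention-to-treat protocol" and then applies a post-randomisation adherence condition framed for one arm only. Confidence in that is high.

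Confidence in the consequence is lower. The bias can be nil, is plausibly toward the diet, and could reverse. With 2 to 4 of 20 diet patients removed, the range is about 0 to 0.75 PG-SGA points, with type I error from 5% to about 10%. The upper end requires early stopping to be strongly related to the week-8 outcome. The number removed, the strength of selection and the correlation of 0.5 are all assumptions. The main damage is the loss of a randomised comparison under a label that says otherwise.

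**What to change.** Replace the sentence with: *The primary (intention-to-treat) analysis includes all randomised patients in the arm to which they were allocated, whatever their diet adherence or duration.* Use any 2-week condition only in a labelled sensitivity or per-protocol analysis, reconciled with the Exclusion criteria section and with its application to controls stated.

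Two additions are needed for this to work:

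- State that patients who stop the diet or fall below the adherence threshold are still asked, where they consent, to attend the week-8 assessment already planned. The Exclusion criteria section now says they are excluded from the study. The Data management section mentions a list of outcome data for patients who discontinue or deviate, but does not say that week-8 measurements are taken.
- Do not fill their missing outcomes with the variable mean. Use a likelihood-based model or multiple imputation that includes baseline. These methods handle stopping that depends on observed data. They do not remove bias when stopping tracks the unmeasured outcome, so the week-8 measurement matters most.

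The cost is a few sentences, somewhat more follow-up and analysis effort, and an estimate that may be less favourable to the diet. The planned 20 per arm is unchanged. Enrolment had already begun when the article appeared, so the set should be fixed before outcome data are examined by arm.

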### Sample size calculation

The sample size required for the current study was calculated using the formula (*n* = 2 [(*z*1−*α*/2 + z1−*β*)^2^ · *s*^2^]/*d*^2^), which has been proposed for parallel clinical trials [24]. Considering the nutritional status (score obtained from the PG-SGA questionnaire) as the key variable [25], type I error of 5% (*α* = 0.05), type II error of 20% (*β* = 0.20, study power = 80%), standard deviation of PG-SGA score (*S*= 4.1), and *d* as equal to 3.9 [25], the required sample size for each group will be 17 patients. However, to ensure a sufficient sample size at the end of the study and taking into account the 15% probable dropout, 20 patients in each group will be recruited according to the inclusion criteria. Considering that the samples will be given in this project are among the patients referred to the radio-oncology clinic and introduced by the radio-oncology specialist, therefore, while ensuring the correct selection of samples based on the inclusion criteria, the number of patients is sufficient to reach the desired sample size for this research project.

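### Filling missing outcomes with an unspecified mean gives a standard error that is too small (arm mean) or an effect shrunk toward zero (overall mean) at the planned 15% dropout

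*Protocol article*

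**What the plan says.** The Statistical analysis section of the protocol gives one rule for missing data: "the mean of each variable will be used to replace missing data". It names no other method and no sensitivity analysis for missing data, and it does not say over which patients the mean is taken.

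The same section defines the main analysis set: "all randomized patients who have followed the Mediterranean diet for at least 2 weeks and who have the baseline measurements will be analyzed". A week-8 value is not required, so a patient lost between week 2 and week 8 stays in the set with a filled-in outcome. Primary and secondary outcomes are measured only at baseline and week 8 (Assessment of study outcomes). The planned tests are repeated measures ANOVA with a time-by-intervention term and, in addition, ANCOVA on the changes with baseline as covariate.

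The Sample size calculation section expects missing outcomes: "taking into account the 15% probable dropout, 20 patients in each group will be recruited". The Exclusion criteria section lists who leaves the per-protocol analysis. The list includes patients who die, patients who withdraw, and "individuals who change their eating route from oral feeding to enteral or parenteral feeding throughout the study".

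**The concern.** Single mean imputation treats an invented value as an observed one. It adds patients to the count without adding information, it removes variance, and it ignores the patient's own baseline, which the plan otherwise uses as a covariate.

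The rule applies to every primary outcome of a 40-patient trial judged at P<0.05. If the arm mean is used, the stated 5% error rate no longer holds. If the overall mean is used, the two arms are pulled together and the estimated effect is too small. Because the text leaves the choice open, it could be made after the data are seen.

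The filled value is also implausible for some patients. The Discussion describes muscle, nutritional status and quality of life as declining continuously in cachexia. A patient who died or withdrew after week 2 would nevertheless be given a mean that comes from those who were measured.

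**Working it through.** **Inputs from the protocol (Sample size calculation).** The "standard deviation of PG-SGA score" is 4.1, and the difference d is taken "as equal to 3.9" points. Alpha is 0.05 two-sided, power 80%, with 17 evaluable and 20 recruited per arm and 15% dropout.

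**Input assumed.** The protocol gives no correlation between baseline and week 8. Values of 0, 0.5 and 0.7 were tried.

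**The plan's own figure.** n = 2 × (1.960 + 0.842)² × 4.1² / 3.9² = 17.35, stated as 17. Inflation for dropout: 17 / 0.85 = 20.0. This reproduces the plan to within rounding. The planned loss is 0.15 × 20 = 3 patients per arm.

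**Arm mean, 3 of 20 missing at random per arm, simple t-test.**
- True SE of the difference, since only 17 values per arm carry information: 4.1 × √(2/17) = 1.406.
- Reported SE. The filled values add nothing to the sum of squares (16 degrees of freedom per arm), but the software divides by 19 and counts 20 patients: 4.1 × √(16/19) × √(2/20) = 1.190.
- Ratio 1.190 / 1.406 = 0.846, so the reported SE is about 15% too small.
- The critical value on 38 degrees of freedom is 2.024, which acts as 2.024 × 0.846 = 1.71 on the true 32 degrees of freedom. Type I error is 0.096.
- With fewer or more filled values per arm: 1 gives 0.063, 2 gives 0.078, 4 gives 0.118, 6 gives 0.173.

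**Overall mean, 3 of 20 missing at random per arm.** Both arms receive the same filled value M. Each arm mean becomes (17 × observed mean + 3 × M) / 20, so the difference is multiplied by 17/20: 3.9 × 0.85 = 3.315 points.

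**Simulation of the planned tests (40,000 trials per case, 3 missing at random per arm, correlation 0.5).**

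| Handling | ANCOVA: true SD of estimate | ANCOVA: mean reported SE | Type I error, ANCOVA | Type I error, time × group | Estimate when truth is 3.9 |
|---|---|---|---|---|---|
| Observed cases only | 1.235 | 1.228 | 0.050 | not run | 3.89 |
| Arm mean | 1.264 | 1.064 | 0.094 | 0.069 | 3.91 |
| Overall mean | 1.078 | 1.065 | 0.051 | 0.051 | 3.32 |

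For correlations 0 to 0.7, arm-mean type I error is 0.094 to 0.096 for ANCOVA and 0.067 to 0.069 for time × group. Other runs of the same ANCOVA case gave 8.8% to 10.0%.

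**Informative, unequal loss.** This scenario is assumed; the protocol does not describe it. The true effect is 0, the correlation is 0.5, the worst patients tend to be lost, and 5 are missing in one arm and 1 in the other (6 of 40, which is 15% in total).

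| Handling | False difference, points | Type I error, ANCOVA |
|---|---|---|
| Observed cases only | 0.90 | 0.136 |
| Arm mean | 1.12 | 0.26 |
| Overall mean | 0.94 | 0.17 |

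Most of the bias is therefore already there before any filling (0.90 of 1.12 points). Arm-mean filling adds some bias and nearly doubles the error rate through false precision. The direction depends only on which arm loses more patients.

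**The case against.** Several points on the other side stand.

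- The wording mentions no arm, so its plainest reading is the overall mean. A reader might infer that the p-values are wrong under any reading, even with data missing completely at random. That is not supported: with the overall mean and random loss, type I error stays at 0.048 to 0.051. Power also falls little: 84.7% against 86.4% for observed cases (ANCOVA, correlation 0.5). The estimate and its interval are still biased toward zero.
- The protocol names repeated measures ANOVA first, and there the arm-mean inflation is modest, about 7%. The 9–10% belongs to ANCOVA.
- A reader might take the exclusion list as the list of reasons for missing outcomes. It defines who leaves the per-protocol analysis. A patient with low adherence, a changed feeding route or a changed cancer treatment can still give a week-8 questionnaire and blood sample, and the Data management section plans to list outcome data for patients who discontinue or deviate. Only death and withdrawal clearly imply a missing value.
- Patients lost before 2 weeks fall outside the analysis set and are not imputed, so 3 per arm is an upper case for the plan's own dropout.
- A reader might charge the whole bias under informative loss to mean imputation. The second table shows otherwise, and the unequal loss itself is an assumption.

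None of this defends the rule. It is fixed in the text, not left to a later document. The per-protocol analysis does not repair it, since patients who die or withdraw are removed there.

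**Conclusion.** The point holds. As written, the rule gives a wrong result at the plan's own dropout, whichever mean is meant. With 3 of 20 missing at random per arm and an assumed correlation of 0.5:

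- Arm mean: ANCOVA standard error about 15% too small, type I error about 9–10% (about 7% for time × group).
- Overall mean: type I error near 5%, but a true 3.9-point effect estimated as about 3.3.

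These sizes become smaller if some of the dropouts leave before week 2; with 2 filled per arm, the arm-mean t-test error is 7.8%. The arm-mean error rate hardly depends on the assumed correlation. Under informative and unequal loss the documents support only a qualitative statement: arm-mean filling adds false precision and some bias to a bias that observed cases already carry.

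**What to change.** Delete mean imputation. For the main analysis, choose one of these and state it in advance:

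- baseline-adjusted ANCOVA on observed week-8 values, or a likelihood-based mixed model on all observed baseline and week-8 values; or
- multiple imputation with arm, the baseline value of the outcome, cancer site and BMI stratum in the imputation model.

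Add one sensitivity analysis that gives unfavourable (delta-shifted) values to patients whose outcome is missing through death or deterioration. It is needed because the main methods assume data missing at random and do not remove that bias.

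The cost is analysis wording and a little more programming, possible in SPSS, which the plan already names. No extra patients, visits or assays are needed, and the Trial status section says that enrolment is ongoing. Intervals become somewhat wider: in the simulation the reported SE goes from 1.064 with the arm mean to 1.228 with observed cases, about 15% more. That matches the true variability. ANCOVA power on observed cases with 17 per arm is 0.75, 0.86 and 0.96 for correlations 0, 0.5 and 0.7.

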### Assessment of study outcomes

In the current study, the main primary outcome would be nutritional status, fat-free mass, muscle strength, and inflammatory markers including interleukin-6 (IL-6), tumor necrosis factor-alpha (TNF-α), and high-sensitive C-reactive protein (hs-CRP). Moreover, the following variables will be considered as the secondary outcome: serum albumin and total protein, complete blood count (CBC), and quality of life. All primary and secondary outcomes will be assessed at the beginning and end (the eighth week) of the study.

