#### Nutritional status assessment

The nutritional status of individuals will be evaluated by the Patient Generated-Subjective Global Assessment Questionnaire (PG-SGA) [22]. This questionnaire assesses patients’ nutritional status based on information about a person’s medical history and diet history (weight change, food intake, gastrointestinal problems, and physical function) as well as clinical symptoms (body fat loss, muscle loss, and edema). According to the guidelines of the PG-SGA questionnaire, the severity of malnutrition will be defined in three following levels: scores between 0 and 1 indicate well-nourished status (A), scores between 2 and 8 indicate moderate or suspected malnutrition status (B), and scores of ≥ 9 indicate severe malnutrition status (C).

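### A Kolmogorov-Smirnov pre-test on the trial's own data chooses the scale of each outcome and can log PG-SGA, which the trial is sized on in raw points

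*Protocol article*

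**What the plan says.** The rule is in the Protocol article, Statistical analysis. It opens with a test, "First, we will apply the Kolmogorov-Smirnov test to determine the normality of variables", and gives the consequence: "In case of the non-normal distribution of a variable, a logarithmic transformation will be conducted". No variable is exempt and no offset for zeros is given. The section does not say whether the test is run on pooled data or by arm, at each visit or once per outcome, or with or without the Lilliefors correction for an estimated mean and SD.

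The non-parametric alternative is named only for a test that "will be used to compare the baseline values" of the two groups. For the outcomes, "we will apply repeated measures ANOVA, in which the effect of time, intervention, and time*intervention interaction will be explored", and changes are compared "using an analysis of covariance, in which the baseline values will be considered as covariates". There are two measurement times: "All primary and secondary outcomes will be assessed at the beginning and end (the eighth week) of the study" (Assessment of study outcomes).

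Two other sections bear on PG-SGA. Nutritional status assessment starts the scale at zero: "scores between 0 and 1 indicate well-nourished status (A". Sample size calculation treats the PG-SGA score as the key variable and works in points, with a "standard deviation of PG-SGA score" of 4.1 and a difference of 3.9.

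**The concern.** A log transformation changes what is estimated: a difference in means becomes a ratio of geometric means. Under the stated rule that choice is made separately for each primary outcome, after the data are in, by a significance test on about 34 to 40 values. The test also examines the wrong quantity. ANOVA and ANCOVA rest on the distribution of the residuals, not on that of the raw variable.

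Three consequences follow from the wording:

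- PG-SGA, the sizing outcome, can be moved to a scale on which d = 3.9 and SD = 4.1 have no meaning, and on which a score of 0 has no value.
- Skewed markers can stay raw because a test at this sample size misses moderate skew.
- Nothing requires the two visits of one outcome to share a scale, although a time effect, a change score and a baseline covariate are hard to interpret otherwise.

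At stake are the interpretation of the primary results and some power on the three inflammatory markers.

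**Working it through.** **1. The plan's own figure.** Inputs from Sample size calculation: two-sided α = 0.05, power 80%, S = 4.1, d = 3.9.

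n = 2(1.960 + 0.842)² × 4.1² / 3.9² = 2 × 7.849 × 16.81 / 15.21 = 17.35 per group.

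The plan gives 17, and 17 / (1 − 0.15) = 20 recruited. The figure is reproduced, and it is in raw points.

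**2. What a log does to that target.** The same 3.9 points is no fixed effect on a ratio scale. With an assumed control mean of 12 the ratio of means is 8.1/12 = 0.68. With a control mean of 8 it is 4.1/8 = 0.51. The documents give no PG-SGA mean, so the sample size calculation does not carry over to logs. log(0) is undefined.

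**3. How the test behaves on a skewed marker.** Assumptions not in the documents: log-normal data, log-SD as shown, baseline to week-8 correlation on the log scale 0.5 to 0.7, 5% test, N = 40, 20,000 replicates. Simulated 5% critical values of the K-S distance are 0.138 (Lilliefors) and 0.210 (uncorrected).

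| log-SD | Flagged at one visit: Lilliefors | Flagged at one visit: uncorrected | Visits disagree: Lilliefors | Visits disagree: uncorrected |
|---|---|---|---|---|
| 0.5 | 62% | 7% | 41-45% | 12-13% |
| 0.7 | 86% | 25-26% | 22-24% | 32-36% |
| 1.0 | 98% | 64-65% | 3-4% | 39-44% |

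The two right-hand columns matter only if the test is run separately at each visit. The wording allows that but does not state it. At N = 34 a log-SD of 0.5 is flagged in about 53% (Lilliefors) or 5% (uncorrected).

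**4. Power under the rule.** Same data model, correlation 0.6, 17 and 20 per arm, true effect set to give about 78-79% power for ANCOVA on the log scale, log-SD 0.5 to 1.0, 20,000 trials per setting.

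- Lilliefors form: 75-79%, a loss of about 0-3 points.
- Uncorrected test: 67-77%, a loss of about 2-11 points.

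The ranges depend on how a flag is turned into a scale, for example by the baseline flag, by a flag at either visit, or visit by visit. Logging only when both visits are flagged leaves more trials raw, so it would do worse. In a further simulation of the rule, Type I error stayed at 4.5-5.1%.

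**5. PG-SGA.** Assumptions not in the documents: negative binomial shape, SD 4.1, control mean 8 to 12, arms 3.9 apart, 20 per arm. The test calls for a log in about 23-51% of trials with Lilliefors and in 0.3-2% uncorrected. At least one zero among 40 patients occurs in 8% of trials at a control mean of 12 and in 97% at a control mean of 8, where the treated mean is 8 − 3.9 = 4.1.

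To see what drives the rejections, take normal arms 3.9/4.1 = 0.95 SD apart and pool them. Lilliefors then rejects in 4.9%, its nominal level. Rounding to integers raises this to 15%. The remainder comes from the assumed skew, not from pooling the arms.

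**The case against.** The case against is that this is ordinary analysis-plan detail with little effect. Much of it limits the point, in five ways.

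- **Power.** A reader might infer that marker power falls to 53-56%. That is the power of ANCOVA kept raw in every trial at log-SD 1.0 (72% at 0.5 and 65-67% at 0.7). It is not power under the rule. At log-SD 1.0 the Lilliefors test flags nearly every sample, so the marker is logged. Type I error is not inflated.
- **Mismatched scales.** A reader might infer that the plan puts baseline and week 8 on different scales. It does not say so. The section also uses the word variable for an outcome as a whole, and the planned models presuppose one scale. The mismatch is a reading that the wording leaves open.
- **Zeros.** A reader might infer that a zero PG-SGA is almost certain. The 97% figure needs a treated mean near 4. Entrants have cachexia by GLIM criteria and are on radiotherapy or chemotherapy, so a zero is unlikely at baseline and only somewhat more plausible at week 8. At arm means of 12 and 8.1, a zero and a Lilliefors rejection coincide in 1.4% of trials.
- **PG-SGA and the form of the test.** With the uncorrected test, PG-SGA would hardly ever be logged.
- **Scope.** A separate analysis plan may exist and could name the scales. But the protocol is not silent here. It states a decision rule, and that rule conflicts with its own sample size basis.

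What survives is that a test on the trial's own data sets the scale of each primary outcome, with nothing to keep PG-SGA in points.

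**Conclusion.** The point holds as a cheap improvement, not as a threat to the trial's validity. The rule lets a marginal normality test choose between a difference and a ratio for every primary outcome, and it can take PG-SGA off the scale on which the trial was sized. That conflict stands on the text alone, however rare zeros are. The marker losses (0-3 points with Lilliefors, 2-11 uncorrected) and the PG-SGA log rates (23-51% or 0.3-2%) rest on the assumed distributions. They also depend heavily on which form of the test is used, which the protocol does not state.

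**What to change.** Remove the Kolmogorov-Smirnov test as the rule for choosing a scale, and name the scale of each outcome in the Statistical analysis section:

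- hs-CRP, IL-6 and TNF-α: natural logs at both baseline and week 8, reported as geometric mean ratios with confidence intervals.
- PG-SGA: raw points, matching the sample size calculation.
- Fat-free mass, handgrip strength, albumin, total protein, quality of life and the other outcomes: untransformed.

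Check the ANCOVA residuals instead of the raw variables, and add a rank-based ANCOVA or a bootstrap interval as a sensitivity analysis only.

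This removes any chance of mixed scales and any need to take the log of a PG-SGA of 0. It costs a few sentences and one sensitivity analysis. The downside is that marker effects are reported as ratios rather than in original units. The sample size stays at 17 per group, 20 recruited.
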